#### Data analyses

The data will be entered into an Excel workbook on password-protected computers, and later exported into SPSS v25 (IBM Corp, Armonk, NY, USA) and SAS v9.4 (SAS Institute, Cary, NC, USA) for statistical analyses. Baseline demographic and clinical characteristics of participants will be summarised by trial group allocation. Treatment evaluation of the primary outcome (i.e. mobility or distance covered during the 6-min walk test) will be performed on the principle of intention to treat, using data collected from all randomised participants. Data will be analysed using random effects mixed models with repeated measures, to account for the non-independence of measurements on the same participant. Models will incorporate as fixed effects the trial group allocation (20 vs 25 Hz), time-point (assessment II, III, or IV), and their interactions as fixed effects, as well as the participant’s GMFCS level; in addition, the baseline value of the outcome variable will be included as a covariate. There will be no imputation of missing data, as based on our previous studies, we expect very limited or no loss to follow-up. Nonetheless, for a small subset of secondary outcomes, such as certain functional tests on the Leonardo platform that cannot be performed by participants with GMFCS level III, only subgroup analyses will be carried out including solely participants with GMFCS level I-II. Model-adjusted differences between randomization groups and within groups (including the potential effects of treatment duration) will be calculated and reported with 95% confidence intervals. All statistical tests will be two-sided at *p* < 0.05, without adjustments for multiple comparisons.

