### Randomization

Randomization will be performed immediately after the initial assessment using an online random number generator available at https://www.randomizer.org. Participants will be allocated to either group 1 (VT frequency 20 Hz) or group 2 (VT frequency 25 Hz). The same member of the research team will enrol participants and assign them to the intervention group. Given that the current study is part of a PhD project, all the procedures (i.e., randomisation, testing, VT sessions) will thus be run by the same member of the research team, making the blinding of the researchers unfeasible in this study. Additionally, the vibration frequencies produced by the Galileo™ vibration platform are readily observable by both researchers and study participants, which makes it unfeasible to ensure blinding not only at the randomization but the intervention stage as well.

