### Clinical assessments/data collection

All participants will have four assessment visits at the Maurice and Agnes Paykel Clinical Research Unit (Liggins Institute, The University of Auckland) (Fig. 1b): 1 – baseline (T0), 2–12 weeks after the lead-in period (control) (T1), 3 – after 12 weeks of vibration therapy (T2), 4 – after completing 20 weeks of vibration therapy (T3). During the first visit, written informed consent will be obtained from a participant’s parent/guardian and, if possible, a child assent form from participants older than 7 years old. Information on demographic, ethnicity, medical history (including the history of birth, comorbidities, previous surgery, Botox injections, injuries, and admissions to the hospital) and medications currently taken will be recorded. We also will collect information on the frequency and duration of activities children undergo at school (e.g., physical education classes) and out of school (e.g., swimming, horse riding, walking with a dog, etc.). The procedures will be similar for all four visits and will also include anthropometric measurements, resting blood pressure and heart rate, mobility, body composition, muscle function, physical activity, gross motor function and respiratory function assessments, and the quality-of-life questionnaire.

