### Respiratory function

The respiratory function will be tested using a CareFusion MicroLab MK8 spirometer (Care Fusion; Chatham, Kent, UK). Before each measurement, the spirometer will be calibrated. Participants will be rested for 10 min before measurements. Before starting the test, subjects will be instructed on the test procedure, which will then be demonstrated by a researcher. A nose clip will be used during the test. Participants will perform a maximum forced inhalation (instructions: “Breath in as hard as you can”), followed by a powerful, quick, forced expiration (instructions: “Breath out as fast and as hard as you can”). At least three technically appropriate measurements will be performed, with the best result taken for statistical analysis. Measures will include forced vital capacity (FVC) (L), forced expiratory volume in 1 s (FEV1) (L), and ratio FEV1/FVC.

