### Physical activity

An activPAL™ accelerometer (PAL Technologies Ltd., Glasgow, UK) will be used to assess participants’ free-living physical activity over 5 consecutive days following their assessment [62]. A 5-day monitoring period was chosen following Ishikawa et al.’s (2013) recommendations, who validated activPAL™ as a reliable measurement tool for children with CP GMFCS levels I–III age 2–14 years old [63]. ActivPAL™ will be attached to the mid-thigh of the dominant leg using a waterproofed dressing. A member of the research team will follow up with families via phone or email in 2 days (36–48 h) after the assessment visit to ensure there are no concerns or issues with the device being used. The average number of steps per day, as well as time of sitting/lying/stepping activities, will be analysed.

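### Because T0 enters the model only as a covariate and imputation is ruled out, a child without a T0 value loses all later readings of that outcome; this is a minor, avoidable loss of precision, mainly for physical activity

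*Protocol article*

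**What the plan says.** Three statements in the Data analyses section act together.

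- **Responses.** The fixed effects include "time-point (assessment II, III, or IV), and their interactions as fixed effects", with allocation as the other factor. T0 is therefore not a response.
- **Role of T0.** "in addition, the baseline value of the outcome variable will be included as a covariate. There will be no imputation of missing data". The section on clinical assessments defines baseline as T0, the visit before the 12-week lead-in.
- **Missing data.** The rule against imputation comes with its reason: "There will be no imputation of missing data, as based on our previous studies, we expect very limited or no loss to follow-up".

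The only exception concerns certain functional tests that children at GMFCS level III cannot do, which are analysed in levels I-II only.

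Two measurement sections show how T0 could be absent while later visits are present. The Randomization section says "Randomization will be performed immediately after the initial assessment", whereas the activity monitor is worn "over 5 consecutive days following their assessment". For spirometry, "At least three technically appropriate measurements will be performed", and eligibility starts at age 5.

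**The concern.** A likelihood-based mixed model tolerates a missing response but not a missing covariate: it drops the record. T0 is the same covariate value for all three of a child's records, so one missing T0 reading removes T1, T2 and T3 together for that outcome. The reason given for not imputing is low loss to follow-up. That concerns later visits and does not cover a missing first reading.

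At stake is precision. Readings taken during vibration would be discarded for both the 20 vs 25 Hz contrast and the within-group change on therapy. The Discussion presents within-child comparison as a main advantage of the design, and a child with T1, T2 and T3 has exactly that information.

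**Working it through.** **Inputs.** From the documents: 24 children per group (48 in all), four visits at weeks 0, 12, 24 and 32. The plan gives no T0 missing rate and no visit correlations, so there is no figure to reproduce. Assumed: share *m* of children without T0 = 5%, 10%, 20% or 30%, missing completely at random; T1 to T3 complete; equal variances; correlation 0.5 to 0.85, either equal between all visits or decaying with time (ρ per 12 weeks).

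**Step 1: does the model drop these children?** In one simulated data set of 48 children with 5 T0 values removed, the planned model on complete rows used 43 children and 129 of 144 records. The 15 lost records are 5 × 3.

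**Step 2: records lost per outcome.**

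| T0 missing | Children of 48 | T1-T3 records of 144 | T2-T3 records of 96 |
|---|---|---|---|
| 5% | 2 | 6 | 4 |
| 10% | 5 | 15 | 10 |
| 20% | 10 | 30 | 20 |
| 30% | 14 | 42 | 28 |

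**Step 3: standard error of the T3 group difference.** Let *n* = 24, S the 3 × 3 correlation matrix of T1 to T3, and S_c the same matrix conditional on T0.

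- Planned model, children without T0 dropped: Var = 2(1 − r²) / [n(1 − m)], with r the T0-T3 correlation.
- T0 as a response with equal group means: Var = the T3 diagonal element of (2/n)[(1 − m)S_c⁻¹ + m S⁻¹]⁻¹.

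With equal correlation ρ, the second expression becomes (2/n)[λ/3 + 2(1 − ρ)/3], where 1/λ = (1 − m)/[(1 − ρ)(1 + 3ρ)] + m/(1 + 2ρ).

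Example, ρ = 0.5 and m = 0.20:

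- Planned: 2 × 0.75 / (24 × 0.8) = 0.0781, SE 0.2795.
- Alternative: 1/λ = 0.8/1.25 + 0.2/2 = 0.74, so λ = 1.351. Var = (2/24)(0.4505 + 0.3333) = 0.0653, SE 0.2556.
- Ratio 0.2795/0.2556 = 1.094.

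Ratio of standard errors, planned over alternative:

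| T0 missing | Equal, ρ 0.5 | Equal, ρ 0.7 | Equal, ρ 0.85 | Decaying, ρ 0.5 |
|---|---|---|---|---|
| 5% | 1.021 | 1.016 | 1.013 | 1.025 |
| 10% | 1.043 | 1.034 | 1.026 | 1.053 |
| 20% | 1.094 | 1.073 | 1.055 | 1.116 |
| 30% | 1.155 | 1.121 | 1.090 | 1.192 |

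**Step 4: standard error of the within-group T1 to T3 change.** Under equal correlation, T0 carries no information on this change, so the ratio is 1/√(1 − m): 1.026, 1.054, 1.118 and 1.195. With decaying correlation (ρ 0.5) it is 1.025, 1.052, 1.114 and 1.189.

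**The case against.** The strongest reply is that a repeated-measures model with baseline as a covariate is standard and valid, and that a missing secondary-outcome baseline is the kind of detail an analysis plan settles. The article never says that such children are deleted, and its use of this model for secondary outcomes is implied rather than stated. This stands in part. However, the article is not silent: it fixes the responses, the covariate and the ban on imputation, and an analysis plan that follows that wording inherits the loss.

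Safeguards also count. Families are contacted 36-48 h after the visit about the monitor, which falls inside the 5-day wear period. Spirometry is preceded by instruction and demonstration, there is no stated cap on attempts, and only children who can follow instructions are eligible. The Discussion's examples of tests that some children cannot do are force-plate tests, not activity or spirometry. Missing T0 values may therefore be few, and at 5-10% the loss is small.

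Two stronger readings are tempting, and the documents support neither:

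- **That the reported change on vibration is biased by a calculable amount.** This would need an assumption about how the dropped children respond, and nothing in the documents supplies one.
- **That T0 activity lost after randomisation biases the 20 vs 25 Hz comparison.** The T0 monitor is worn in the first days of the lead-in, when both groups continue usual care and no child has received vibration. The loss cannot result from either frequency. A failed T0 spirometry test precedes allocation altogether.

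**Conclusion.** The point holds as a minor matter of precision. The loss is outcome by outcome: a child without T0 activity still counts for the 6-minute walk test. That primary outcome is practically untouched, because it is measured at the visit that precedes randomisation, and the intention-to-treat sentence names only the primary outcome.

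For the exposed secondary outcomes, the unnecessary increase in standard error runs from about 1-3% (group difference at T3) and 3% (within-group T1 to T3 change) at 5% missing, to 9-19% and 19-20% at 30% missing. These figures rest on the assumed missing rates, on T0 missing completely at random and on correlations of 0.5 to 0.85. Which end applies cannot be told from the documents.

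**What to change.** In the Data analyses section, replace the baseline covariate by T0 as a response: time-point = assessment I, II, III or IV, with the two group means constrained equal at assessment I, GMFCS level kept, and no imputation. Read the group differences at T2 and T3 and the within-group changes from that one model.

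The equal-means constraint is justified by randomisation. It also suits activity recorded just after allocation, since both groups are then under usual care. Every child with any reading of an outcome is kept, and the sponsor's rule against imputation is respected. With complete T0 data the results are practically those of the planned model.

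The cost is one sentence of analysis wording and a re-coded data set, with no new data, children or staff. It is a free improvement.

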### Intervention

Following the control period, a 20-week intervention period will start. It will consist of 4 vibration sessions a week performed on Galileo Basic vibration plates (Novotec Medical, Pforzheim, Germany). Participants will start from three 1-min bouts of vibration training at the frequency of 12 Hz with a gradual increase of both frequency and duration over the first 4 weeks to achieve the target frequency and time (3 sets of 3 min vibration training alternating with 3-min breaks between them). The target frequency of the vibration will vary depending on the intervention group (either 20 Hz or 25 Hz) and will be maintained for the remainder of the intervention period. Other parameters will be kept comparable in both treatment groups: amplitude – 2-4 mm, acceleration – maximum 11.4 g. Participants will stand barefoot on the plate with knees slightly bent, back straight, and arms free. For participants with poor balance, an adjustable metal frame will be used for safety purposes.

The vibration therapy frequencies (20 Hz vs 25 Hz) have been selected based on current literature and the Galileo vibration platforms manufacturing specifications. According to the latter, the main effect of low frequencies (12–20 Hz) lies in an improvement of muscle function and coordination whereas high frequencies (more than 20 Hz) have an impact on muscle power and muscle force [42]. According to the literature, 20 Hz is a typically recommended frequency for children with cerebral palsy [43]. In addition, 20 Hz has been shown to be the safest of low frequencies due to low vibration transmissibility to the head [19] and better coordination and posture stabilisation during the vibration training sessions [44]. 25 Hz was chosen as it is the highest frequency that has been used in long-term studies of side-alternating vibration training that involved children with cerebral palsy and that has demonstrated no severe adverse effects [24]. To summarize, the two frequencies were selected since they provide the optimal combination of expected results, as informed by extant literature and equipment specifications, and adherence to the ethical obligation of not compromising the patients’ safety.

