### Primary outcome

The primary outcome measure is mobility, which will be assessed by the distance walked in the 6-min walk test (6MWT) at four-time points: baseline, in 12 weeks (the end of the control period), after 12 weeks of vibration therapy, and after completing 20 weeks of vibration therapy (Fig. 1b).

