### Statistical considerations

#### Sample size

The sample size calculation was performed in GPower software version 3.1.9.2. For the calculation, we used the mean and standard deviation obtained in the 6MWT from the clinical trial performed of 40 participants with cerebral palsy [14]. Setting the level of statistical significance at 0.05 and power at 0.95, a minimum size of 44 participants for two groups was found. Considering a 10% drop-out rate, the final sample will include 48 participants in total, with 24 for each intervention group.

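### No primary visit or contrast is fixed for the 6-minute walk test, and all its contrasts are tested at 0.05 unadjusted, so the 5% error rate does not hold for the primary outcome

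*Protocol article*

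**What the plan says.** Under Primary outcome, the article defines a measure and its visits: "The primary outcome measure is mobility, which will be assessed by the distance walked in the 6-min walk test (6MWT) at four-time points". The visits are baseline (T0), the end of the lead-in (T1, week 12), and after 12 and 20 weeks of vibration (T2, week 24; T3, week 32).

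Data analyses specifies a mixed model with group, visit (assessments II to IV), their interaction and GMFCS level, adjusted for the baseline value. From it, "Model-adjusted differences between randomization groups and within groups (including the potential effects of treatment duration) will be calculated" and reported with 95% confidence intervals. The testing rule is general: "All statistical tests will be two-sided at" the 0.05 level, "without adjustments for multiple comparisons". It makes no exception for the primary outcome.

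Three other places bear on which question comes first:

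- Sample size: "Setting the level of statistical significance at 0.05 and power at 0.95, a minimum size of 44 participants for two groups was found". This suggests 20 vs 25 Hz.
- Discussion, limitations paragraph: the analysis is described as resting on comparison within the child, lead-in against intervention.
- Abstract and Discussion: 12 vs 20 weeks of therapy is a further stated comparison.

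None of these is ranked above the others.

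**The concern.** One primary outcome is not one primary test. With two groups and three modelled visits, the stated analysis gives several tests on the same outcome, each at 0.05, and nothing says which of them answers the trial's question. The nominal 5% then does not describe the chance of a false positive finding on the primary outcome, and a reader of the results cannot tell which contrast was intended as confirmatory.

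Fixing the contrast in advance matters more here than in a blinded trial. Under Randomization, the article says that the same researcher randomises, tests and runs the sessions without blinding. The Discussion also expects the results to inform treatment guidelines. Leaving secondary outcomes unadjusted is a separate and lesser matter, acceptable if they are labelled as supportive.

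**Working it through.** **1. What the plan's own figures settle.** One contrast fixed in advance and tested two-sided at 0.05 has a 5% error rate. The sample size of 44 cannot be reproduced, because the article gives neither the mean difference nor the standard deviation, only their source ("we used the mean and standard deviation obtained in the 6MWT from the clinical trial performed of 40 participants with cerebral palsy"). Solved backwards at 95% power and two-sided 0.05, 44 corresponds to a standardised difference of about 1.11 for two groups of 22, or about 0.56 for a paired comparison in 44 children. The number 44 therefore does not reveal which test was meant; only the reference to two groups does.

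**2. Does the model pick a primary test by default?** No. Assessment II is T1, before any vibration, so no frequency effect can exist there. A group main effect averaged equally over the three visits would shrink a difference of size D at T2 and T3 to (0 + D + D)/3 = 2D/3. The interaction is a test with several degrees of freedom. Neither is designated as primary.

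**3. Candidate contrasts on the 6-minute walk test.** Group differences at T2 and T3 give 2. The changes T1-T2, T1-T3 and T2-T3 in each of two groups give 3 × 2 = 6, so 8 in all. The group difference at T1, which the model also yields, makes 9.

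**4. Chance of at least one p < 0.05 under no effect and no time trend.** For k independent tests this is 1 − 0.95^k. The contrasts share data, so the chance was also simulated:

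- 20,000 trials per setting, with 22 and with 24 children per group.
- T1 to T3 conditional on T0; pooled-variance t tests, two-sided 0.05.
- Correlation between visits either constant (0.6, 0.8, 0.9) or decaying (0.6, 0.8, 0.9 per 12 weeks). The article gives no correlation, so these values are assumptions.

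| Contrasts counted | k | 1 − 0.95^k | Simulated range |
|---|---|---|---|
| One, fixed in advance | 1 | 5.0% | – |
| Group differences at T2, T3 | 2 | 9.8% | 7.6-9.9% |
| Plus T1-T2, T1-T3 in each group | 6 | 26.5% | 19.8-24.5% |
| Plus T2-T3 in each group | 8 | 33.7% | 25.5-28.9% |
| Plus group difference at T1 | 9 | 37.0% | 27.8-30.9% |
| Plus three group-by-time contrasts | 12 | 46.0% | 30.3-33.1% |

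Simulation error is small: for a rate of 29% it is √(0.29 × 0.71 / 20,000) ≈ 0.3 percentage points.

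**5. Direction of the main simplification.** The simulation assumes no change over time. The children are 5-12 years old and are followed for 32 weeks. Growth or familiarity with the test would make within-group changes significant more often than shown.

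**6. Time at target frequency.** Frequency and session time are built up "with a gradual increase of both frequency and duration over the first 4 weeks". By T2 that leaves 12 − 4 = 8 of 12 weeks at target (67%), and by T3 20 − 4 = 16 of 20 weeks (80%).

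**The case against.** Only a journal article is available, and a primary visit and hierarchy of contrasts may stand in a SAP that is not shown. That is fair, and the point is proven for the article alone. But the article does more than leave a detail out. It rules out adjustment for every test, in the same paragraph that lists the contrasts, and its sections point to different primary questions.

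The family of contrasts is also not the article's. Nowhere does it say that any single significant contrast makes the trial positive. Frequency and duration can be seen as separate questions, and whether they form one error family is a matter of judgement. The count could also be drawn differently: it leaves out the contrast that a lead-in design implies, change during therapy against change during the lead-in. This stands. It is why the result is given as a range with the family stated, and why the narrowest family, the randomised comparison at two visits, is shown separately.

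Two stronger readings are tempting. One is that the trial's false-positive rate is about 30%, or is capped there. The article declares no such decision rule, and 12 contrasts already give 30-33%, so the figure is neither the trial's error rate nor a ceiling. The other is that the authors mean to choose the primary result after seeing the data. The text leaves that open but says nothing of the kind, and it commits to reporting the differences with confidence intervals.

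Finally, naming the between-group contrast chooses the question for the trial team. That also stands in part: the text must be reconciled whichever question is chosen.

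**Conclusion.** The point holds as a defect in what the article fixes: a single primary outcome, no primary visit or contrast, and an explicit rule of no adjustment across all tests on it. Against 5% for one fixed contrast, the chance of at least one p < 0.05 is about 8-10% for the two randomised comparisons after the start of therapy, and about 25-31% if the within-group contrasts count as well. These figures rest on an assumed family of contrasts, assumed correlations between visits, and no time trend. The defect itself depends on none of them. It should be corrected, and the correction is cheap. The sample size of 44 is neither confirmed nor refuted by this check.

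**What to change.** Amend Primary outcome and Data analyses, in the protocol or SAP and before outcome data are examined, to name one primary contrast and one visit. Then make Sample size and the Discussion agree with it.

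The natural choice is the baseline-adjusted 20 vs 25 Hz difference in 6-minute walk distance at T3 (week 32), two-sided 0.05. It is the randomised comparison, matches the two-group sizing, and comes after the longest exposure at target frequency. Sample size should then state the difference, standard deviation and test behind the 44, since 22 per group at 95% power implies a standardised difference of about 1.11 between the two frequencies. If the trial team instead means the within-child comparison, it should say so and restate the sizing for that test.

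Label the T2 difference, the own-control and duration contrasts and all secondary outcomes as supportive, reported with the 95% confidence intervals already planned.

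If the own-control effect of vibration is also to be confirmatory, test the two with Holm. The first Holm step uses 0.05/2 = 0.025. At a standardised difference of 1.11 and 22 per group, power for the between-group test would fall from 95% to no lower than about 91%.

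The cost is a few sentences across four sections, no extra visits or data, and fewer results that can be called confirmatory.
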